Seven Mindfulness Skills for Students courses run in parallel each term (which only lasts 9 weeks in Cambridge) with up to 30 students each. Students need to choose a session time and day to attend each week but are encouraged to attend as many sessions as they can, so if they cannot make their usual session, they can attend an alternative session within the same week (session hopping). Students are contacted by email when they miss a session to check whether the absence is related to a negative experience with mindfulness and, subsequently, to offer support.

As this will be a pragmatic study, care will be taken not to interfere with or modify routine practices for intervention delivery. Therefore, there will be no ad hoc adherence optimisation procedures. Participants in the control group will be guaranteed a space in the following year's mindfulness course and will be requested to inform the research team should they decide to learn mindfulness elsewhere during the follow-up period.

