### Sample size

The minimum sample size required was calculated to detect a 0.3 SD change in psychological distress with CORE-OM, the primary outcome. This change constitutes a small difference, but is reasonable for a relatively short mindfulness course, and attractive if this shift happens at a community rather than a clinical level.^20^

A study of a non-clinical sample (746 students from two UK universities plus a community sample of 360 people) found a mean total score of 0.76 points and a SD of 0.59 points.^21^ To detect a change of 0.3 SDs at p<0.05 with 90% power, 550 students (275 per arm) are estimated to be needed, allowing for 20% loss to follow-up as informed by previous studies (eg, Warnecke *et al*^22^).

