### Blinding and randomisation procedures

After agreeing to take part, students will be emailed with a link to the online baseline questionnaire. Only those who complete the baseline questionnaire will be randomised. Simple randomisation will be carried out remotely by the survey software (Qualtrics) using computer-generated random numbers. Participants will be informed of their allocation automatically after completing the baseline questionnaire. This way the allocation process will be concealed from researchers.

Participants randomised to the intervention group will be requested to state which of the seven mindfulness session times on offer they would be able to attend. Then, to minimise attrition, an allocation optimisation programme will be run with these data to assign as many students as possible to one of their preferred course times.

Participants cannot be blind to allocation because of the nature of the intervention. However, outcome assessment will be blind because data collection is carried out remotely and automatically. The primary analysis will be carried out by a statistician blind to which arm is the intervention, and other variables/information which could be used to identify intervention arm data. Mindfulness courses will include participants who are not part of the trial (consisting of up to 60 interested students distributed evenly across courses so that 4–5 students out of 30 per course are not part of the study), and the mindfulness teacher will not be told who is and who is not a participant in the study.

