By degree, as most have examinations during the examination term but some do not;By year of study, to explore whether results differ for last year students, a different subpopulation as control group final year students will not be offered mindfulness a year later;By baseline CORE-OM: those initially worse may drive change;By gender: there is evidence of differential impact;^10^By amount of home practice during and after course in intervention group participants;By prior meditation experience (prior 8-week course or +50 hours spent meditating in the past—an 8-week course translates into 10–50 hours) as only novices may experience a change.

In order to assess how our sample compares against the student population in the UK, demographic and normative well-being/distress data will be obtained from the literature and compared with baseline values in our sample. A comparison of our baseline data with the profile of students attending the University Counselling Service will also be performed where possible to evaluate where our sample lies in the range between community and clinical student samples.

All statistical analyses will be conducted at an α level of p=0.05 (two-sided). Linear mixed models will be used for the analyses. Assumptions will be tested and diagnostic plots will be explored to assess model fit. Descriptive statistics for continuous variables will be summarised using mean/SD and median/IQR. Discrete variables will be summarised by proportions.

It is expected that the clustering effect will be negligible: although this is a group intervention, the work is highly personal, all the courses are taught by the same teacher, each course includes students from different colleges and courses, and the ‘session hopping’ option introduces variability. However, we will compute intraclass correlation by analysing session attendance patterns to see whether there is any clustering effect. If there is one, we will adjust for it using multilevel techniques.

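### Adjustment for course-group clustering in the primary analysis depends on an unspecified data-driven check, and the sample size makes no allowance for clustering

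*Protocol article*

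**What the plan says.** The Intervention section states that "Seven Mindfulness Skills for Students courses run in parallel each term", with up to 30 students in each. The Recruitment section describes two waves, one per term, so there are about 14 taught groups. The control arm has no corresponding grouping.

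Under Statistical methods, the primary analysis adjusts for baseline score, demographics and timing of the course relative to examinations. Course group is not in that list. The section expects clustering to be negligible because the work is personal, one teacher takes every course, groups mix colleges and degrees, and students may switch sessions. It continues: "However, we will compute intraclass correlation by analysing session attendance patterns to see whether there is any clustering effect", and then "If there is one, we will adjust for it using multilevel techniques". It names no test, no threshold and no model for groups that exist in one arm only.

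The Sample size section says: "To detect a change of 0.3 SDs at p<0.05 with 90% power, 550 students (275 per arm) are estimated to be needed". That figure includes a margin for 20% attrition. The section mentions no ICC or design effect.

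On blinding: "The primary analysis will be carried out by a statistician blind to which arm is the intervention". The same section and Data management also keep from that statistician any information that could identify the arms.

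**The concern.** Students taught together may have correlated examination-term CORE-OM scores. If so, the intervention mean is less precise than an independent-observations model reports. The plan leaves this to a check on the trial's own data, which raises four difficulties.

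- With 14 groups, a check can easily miss an ICC large enough to matter. Failing to find one is weak evidence that it is zero.
- Without a threshold, the choice of primary model is made after data are seen.
- The check is tied to attendance patterns. The relevant quantity is the ICC of the outcome by course, and the wording does not make clear that this is what will be computed.
- Course membership exists only in the intervention arm, so supplying it to the blinded statistician reveals the arm.

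At stake are the standard error, confidence interval and p-value of the primary comparison, and the power claimed for it.

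**Working it through.** **Inputs from the protocol.** Difference 0.3 SD; two-sided alpha 0.05; 90% power; 275 per arm; 20% loss (Sample size, Statistical methods). Seven courses per term (Intervention) and two terms (Recruitment) give 14 groups. As a cross-check, Blinding and randomisation procedures allows up to 60 non-trial students at 4–5 per course, and 60/14 = 4.3. The SD of 0.59 cancels because the effect is in SD units.

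**Assumptions, not in the documents.** ICC 0.01 to 0.05; equal group sizes; where used, a baseline correlation of 0.5.

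**Step 1: the plan's own figure.** Evaluable per arm = 2 × (1.960 + 1.282)² / 0.3² = 234. Multiplying by 1.2 gives 281 per arm, 562 in total, within 3% of 550. Taking 550 as given, 275 × 0.8 = 220 completers per arm, and power = Φ(0.3/√(2/220) − 1.96) = 88.2%. Both calculations treat observations as independent, so 550 contains no allowance for clustering.

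**Step 2: clustering in one arm.** Completers per course m = 220/14 = 15.7. Design effect in the intervention arm DE = 1 + (m − 1) × ICC. Variance of the difference in SD units = (DE + 1)/220, so the true SE exceeds the nominal SE by the factor √((DE + 1)/2).

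- Type I error if never adjusted = 2 × [1 − Φ(1.96/√((DE + 1)/2))].
- Power = Φ(0.3/√((DE + 1)/220) − 1.96).
- With baseline correlation 0.5, the variance is multiplied by 1 − 0.5² = 0.75, with the ICC applied to the residual variance.

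| ICC | DE | SE factor | Type I, never adjusted | Power, no baseline adjustment | Power, correlation 0.5 |
|---|---|---|---|---|---|
| 0 | 1.000 | 1.000 | 5.0% | 88.2% | 95.3% |
| 0.01 | 1.147 | 1.036 | 5.9% | 85.9% | 93.9% |
| 0.02 | 1.294 | 1.071 | 6.7% | 83.6% | 92.4% |
| 0.05 | 1.736 | 1.170 | 9.4% | 76.7% | 87.4% |

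These are normal approximations. With Satterthwaite degrees of freedom, the fifth column is about 82% at ICC 0.02 and 74% at 0.05.

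**Step 3: the two-step rule.** Simulation under no treatment effect, with 14 courses of 16 completers against 220 controls. The adjusted test uses the between-course mean square and Satterthwaite degrees of freedom. Because the protocol gives no trigger, two were tried: a 5% F-test for a course effect, and any positive ICC estimate.

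| ICC | F-test detects clustering | Type I, F-test trigger | Type I, positive-estimate trigger | Type I, always adjusted |
|---|---|---|---|---|
| 0 | 5.2% | 4.9% | 4.2% | 5.0% |
| 0.01 | 11.2% | 5.1% | 4.4% | 4.7% |
| 0.02 | 20.2% | 5.7% | 4.8% | 5.0% |
| 0.05 | 49.5% | 6.2% | 5.0% | 5.0% |

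The positive-estimate column comes from 40,000 runs and the others from 20,000. Monte Carlo SE near 5% is √(0.05 × 0.95/20,000) = 0.15 points, and repeat runs differed by a few tenths of a point.

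**The case against.** The case against a serious finding is substantial, and most of it stands.

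- **No test is specified.** A reader might infer that checking first must inflate type I error. That depends on the trigger. If any positive estimate leads to adjustment, there is no inflation. With a 5% F-test, it is about one percentage point at most over this range. The 6.7% and 9.4% figures describe never adjusting, which the protocol does not propose; they would apply only if the check ended in no adjustment.
- **Power.** A reader might infer that the trial is underpowered. The planned primary analysis adjusts for baseline CORE-OM, which could recover much of the loss, and the ICC itself is an assumption.
- **Attendance patterns.** A reader might infer that the wrong ICC will be computed. Because students may switch sessions, attendance could simply define membership for an outcome ICC. The wording is ambiguous and is not shown to be an error.
- **Blinding.** A reader might infer that adjustment is impossible under the blind. The protocol does not say so: an analysis with course identifiers could follow a locked blind step. The passages still need to be reconciled.
- **Reasons for a low ICC.** One teacher, mixed groups and session switching plausibly reduce clustering. They do not show it to be zero. The Intervention section also describes interactive exercises meant to build community within the group, which works the other way.

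The unstated threshold alone could be left to an analysis plan. The conditional structure is different: the protocol itself fixes it, and a better rule is available at little cost.

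**Conclusion.** The point holds at moderate weight: it should be fixed, but it does not undermine the trial. The protocol makes adjustment for course clustering conditional on an unspecified check with low power at small ICCs (about 11% to 49% detection by a 5% F-test at ICC 0.01 to 0.05), and its sample size assumes independence.

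Type I error could lie anywhere from no inflation to about 9%, depending on how the check is read; a formal 5% test gives about 5% to 6%. Power before baseline adjustment falls from 88% to between 86% and 77%; with an assumed baseline correlation of 0.5 it is about 94% to 87%. All of this rests on the assumed ICC range, 14 equal groups and 220 completers per arm. Randomisation is individual, and the question asked by the primary comparison is unchanged.

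**What to change.** - Replace the conditional rule. The primary mixed model always includes a random effect for assigned course in the intervention arm only, with arm-specific residual variances and Satterthwaite or Kenward-Roger degrees of freedom, whatever the estimated ICC.
- Report the ICC of examination-term CORE-OM by assigned course. Use attendance-based membership as a sensitivity analysis for session switching.
- Reconcile this with Blinding and randomisation procedures and Data management: lock the analysis code under masked arm labels, then add the course identifier.
- State power over an ICC range of 0 to 0.05, with and without baseline adjustment.

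The cost is a change of wording and a slightly wider confidence interval. Course assignment is already generated when students are placed in session times, and linear mixed models are already planned. Always adjusting kept simulated type I error at about 5%. The change should be made before the arms are unmasked.

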### Data monitoring and adverse events

An Independent Data Monitoring and Ethics Committee (IDMEC) will be set up comprising an independent chair familiar with student welfare issues, an independent researcher, a representative from the student body and a representative from the colleges that make up the University. Its role will be to safeguard the interests of trial participants, assess the safety and efficacy of the intervention during the trial, and monitor the overall conduct of the trial. The IDMEC will meet three times a year and make recommendations to the researchers; its terms of reference are available on request and include provision for terminating the trial early. There are no plans for interim analyses, although the IDMEC could request them.

Introductory, 8-week mindfulness courses for people who meet our selection criteria are not known to be associated with adverse events. However, we will systematically monitor for such events and have a duty of care to react when there is an indication of extreme distress or risk in a student. Participants will be encouraged on enrolment to look for signs of their mental or physical health deteriorating, whether or not it is related to the mindfulness course. Emergence of such symptoms will be considered adverse events. Subsequently, during the study, there will be three ways of identifying adverse events:
There may be uncomfortable moments during the mindfulness course as participants are requested to turn their attention to whatever thoughts are coming into their minds. They will be taught how to safely deal with these thoughts, but initial experiences can be somewhat distressing. Participants are frequently encouraged to approach the course teacher to discuss any concerns.All participants will complete the CORE-OM questionnaire at baseline, postintervention, during the examination term and at 1-year follow-up. The study team will monitor the risk subscales of CORE-OM each time participants complete it (as stated in the participant information sheet). Studies support using the following cut-off scores as markers of significant risk: 3 or more for the self-harm risk subscale, 3 or more for the harm to others risk subscale, or 5 or more for the suicide risk subscale.^27^
^28^ Scores of 7 or more points in any subscale will be prioritised.All the trial participants will be requested to let the study team know if and why they are planning to leave the study.

In the event of any adverse events emerging, participants will be contacted, strongly encouraged to seek additional help and directed to relevant health services. If a participant fails to respond or refuses to access help without reasonable justification, they will be informed that the research team will try to contact support services (eg, college nurse) without their consent (as stated in the participant information sheet). Events will be recorded on a structured form sent to the IDMEC Chair who will determine whether they could be related to the intervention (ie, adverse reactions^29^) and how to proceed (eg, stopping the trial early).

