Process measures will involve: (1) registering attendance at mindfulness courses (register taken) and asking why sessions were missed (routine practice for UCS); (2) asking students whether they did their mindfulness homework during the course and how much they have practised after the course, including whether they became members of the Mindfulness Society; (3) for students who abandon the study (ie, fail to complete questionnaires or contact us saying they wish to quit the study), information on why they have done so will be requested; (4) participants in the control group will be asked whether they have practised mindfulness elsewhere during the follow-up period.

Apart from the baseline measurements outlined in table 1, the following baseline data will be collected in order to compare the sample with the student population, and to run subgroup analyses: (1) students' prior experience with meditation and mindfulness; (2) demographic data provided by the student registry (eg, disability, ethnicity, socioeconomic classification). All baseline data will be collected before randomisation.

Questionnaires will be web-based. Privacy issues related to accessing student records and collecting data from smartphone sensors were explored in a focus group with students who completed mindfulness courses taught before the trial. Students felt these methods were acceptable.

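### Adverse events are defined as emerging deterioration, but the CORE-OM route identifies them by a fixed risk level that also applies at the pre-randomisation baseline

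*Protocol article*

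**What the plan says.** In the protocol's Data monitoring and adverse events section, participants are encouraged on enrolment to "look for signs of their mental or physical health deteriorating, whether or not it is related to the mindfulness course", and "Emergence of such symptoms will be considered adverse events". The section then announces the means of detection: "Subsequently, during the study, there will be three ways of identifying adverse events". These are concerns raised with the course teacher, the CORE-OM risk subscales, and reasons given for planning to leave the study.

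On the second, the text says "All participants will complete the CORE-OM questionnaire at baseline, postintervention, during the examination term and at 1-year follow-up", and "The study team will monitor the risk subscales of CORE-OM each time participants complete it". The markers of significant risk are absolute scores: "3 or more for the self-harm risk subscale, 3 or more for the harm to others risk subscale", and 5 for suicide risk. Scores from 7 upward in any subscale are prioritised.

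Under Outcomes and data collection, "All baseline data will be collected before randomisation". For adverse events that emerge, the stated response is contact, encouragement to seek help, referral and possible escalation. Then "Events will be recorded on a structured form sent to the IDMEC Chair who will determine whether they could be related to the intervention", and how to proceed, with early stopping given as an example.

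**The concern.** One score threshold is doing two jobs. A welfare alert properly depends on the current level, because a student at risk needs a response whenever the risk began. An adverse event, as this protocol defines it, depends on change. Using the level for both can produce two errors:

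- A student who was above a cut-off before allocation, and stays there, can enter the adverse event record although nothing has emerged.
- A student whose distress rises without crossing a risk cut-off has deteriorated under the definition, but this route raises no flag.

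At stake is the harm record that the IDMEC Chair uses to judge relatedness and the future of the trial. The Introduction also says the evaluation should give a fuller view of positive and negative impact. The primary efficacy analysis is not affected.

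**Working it through.** The protocol gives no computed figure on this point, so the check sets its statements side by side.

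1. **Definition.** Emergence and deterioration both describe change over time, and both mental and physical health are covered.
2. **Questionnaire rule.** Cut-offs of 3, 3 and 5, with priority from 7, are levels. No difference from an earlier score is required.
3. **Timing.** Four completions are named, the first being baseline, and the subscales are checked at each. Baseline precedes randomisation, and no exemption is stated.
4. **Does anything keep high baseline scorers out?** Eligibility criteria are self-reported and contain no score threshold (Eligibility criteria). Allocation is shown automatically once the baseline questionnaire is complete (Blinding and randomisation procedures). A student above a cut-off at baseline can therefore be randomised.
5. **Is there a separate path for welfare alerts?** The only response described is the one triggered by adverse events. Either a baseline exceedance is an adverse event, or the article states no response to it.
6. **Reach of the routes by arm.**
   - Teacher contact: intervention arm only.
   - Missed-session emails (Intervention section, not among the three listed routes): intervention arm only.
   - Reasons for leaving: both arms, but only those who leave or plan to.
   - CORE-OM: everyone in both arms who returns the questionnaire.

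   Only the last is systematic, individual and the same in both arms.
7. **What the efficacy analysis adds.** Statistical methods compares mean CORE-OM by arm, adjusted for baseline, and explores the risk/harm subscale. A difference in means does not count individuals who worsened.

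**Illustration, on assumptions only.** Let p be the share above a cut-off at baseline, and let qc and qi be the risks of a new flag among the rest in the control and intervention arms. Each person is counted once. The documents give none of these values. Take qc = 5% and qi = 10%, a true ratio of 2.0. If baseline flags are counted, the ratio becomes [p + (1−p)qi] / [p + (1−p)qc], and the pre-existing share of control flags is p / [p + (1−p)qc].

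- p = 2% (0.02 × 550 = 11 students): 0.118/0.069 = 1.71; pre-existing share 0.02/0.069 = 29%.
- p = 5% (27.5 students): 0.145/0.0975 = 1.49; pre-existing share 0.05/0.0975 = 51%.
- p = 10% (55 students): 0.190/0.145 = 1.31; pre-existing share 0.10/0.145 = 69%.

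The risk difference among all randomised is (1−p)(qi − qc) whether or not p is added to both arms, so it does not shrink.

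**The case against.** The strongest reply is that nowhere does the protocol say a baseline exceedance is logged as an adverse event. The list of routes is introduced as applying subsequently, during the study. The cut-offs are called markers of risk, and the section invokes a duty of care, so baseline monitoring may be a welfare check only. That reading is open, and the logging of baseline flags is an inference. But baseline is named inside the route for identifying adverse events, and no other response path is described, so the text does not settle the matter.

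A reader might infer that all worsening below the cut-offs is missed. The documents do not support that. The other two routes have no threshold, missed sessions prompt an email, and participants are told to look out for deterioration. What stands is narrower: the CORE-OM route does not flag it, and the other contacts are either confined to the intervention arm or limited to leavers.

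A reader might also infer that the trial cannot detect harm on distress. That is wrong too, because the two-sided primary comparison would detect a net average worsening if it were large enough.

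The Chair can judge a pre-allocation flag unrelated, and no pooled risk ratio is planned. Both points are fair and limit the consequence, although a judgement of unrelated does not by itself remove the record from the count.

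Finally, counting rules are often left to a fuller document. That excuses the missing detail, but not a definition and an identification rule that differ within the same section.

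**Conclusion.** The point holds as an inconsistency between a change-based definition and a level-based identification rule that includes the pre-randomisation baseline. As written, pre-existing or persistent risk can be recorded as an adverse event, and some real worsening is not flagged by the one systematic route common to both arms.

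No reliable size can be attached. A reader might infer from the four completions that a quarter of score-based flags precede treatment (1/4), or 29% with 20% loss at each later completion (1/(1 + 3 × 0.8)). Both figures assume a constant share above the cut-offs, which the documents do not give. The protocol's own description of the examination term as the most stressful period makes constancy doubtful. The shrinkage in the illustration concerns a ratio only and rests on assumed risks. Likewise, a persistently high scorer could contribute up to four records only if each completion is counted separately, and the article does not say.

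The correction is worth making for the harm reporting. It does not bear on the primary analysis.

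**What to change.** Reconcile the definition with the identification rule in the adverse event section:

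- Leave the stated cut-offs and the welfare response unchanged at all completions.
- Log baseline exceedances separately, as pre-existing.
- For adverse event counting and IDMEC reporting, count per person only post-randomisation exceedances that are new or increased relative to the participant's own baseline.
- Add a by-arm table of participants whose CORE-OM total worsened from baseline by more than a prespecified reliable-change limit.

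The cost is protocol wording and one table from data already collected. The limit must be chosen in advance.

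The fix has a gap that should be acknowledged: small rises below the cut-offs remain uncounted. For example, 4 points gained on risk items alone add 4/34 = 0.12 to the total mean score. With the SD of 0.59 from the Sample size section, a conventional 95% reliable-change limit is 1.96 × √2 × 0.59 × √(1 − reliability). That falls to 0.12 only if reliability is about 0.99.
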